### Variables measured and schedule of assessments

The variables measured preoperatively are age, sex, ethnicity, laterality, duration of symptoms, BCVA (Best-corrected Visual Acuity), lens status (either phakic or pseudophakic), macular hole diameter on OCT scans and the Quality of Life VFQ-25 questionnaireThe variables measured at 3 months postoperatively are BCVA, macular hole status (closed; open flat or open elevated), the Quality of Life VFQ-25 questionnaire, subject-reported experience of positioning and, if primary repair of a macular hole failed, was a second operation performed or planned?

For each comparison of outcomes according to positioning policy, the following summaries will be provided (see templates for tables in Additional file 1):The number of patients in each positioning policy group who are included in the analysisA summary measure of the outcome, by positioning policy group (mean and standard deviation (SD) for continuous outcomes, number and percentage in each category for categorical outcomes). The treatment effect (difference in means for continuous outcomes, odds ratio for binary outcomes) with its 95% confidence interval (95% CI) and *p* value

All comparisons will adjust for linear effect of macular hole size (μm) at baseline, phakic lens status at baseline, and a random effect of site (hospital). We will anonymise data reported by hospital site. Outcomes which are also assessed at baseline (BCVA and quality of life) will be analysed adjusting also for a linear effect of the baseline measurement.

Patients have a 2-week postoperative appointment, at which time clinicians may be able to identify that the macular hole closure was unsuccessful, meaning that a second operation to close the hole is required. The outcome of any participant who had a second surgery after randomisation but before the 3-month visit will be imputed as open, as it is most unlikely that the hole will close without further treatment by 3 months. These patients will not be completing secondary questionnaires.

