**Methods/design:**

The PIMS trial is a multicentre, parallel-group, superiority clinical trial with 1:1 randomisation. Patients (*n* = 192) with macular holes (≥400 μm) will be randomised after surgery to either face-down positioning or face-forward positioning for at least 8 h (which can be either consecutive or nonconsecutive) a day, for 5 days following surgery. Inclusion criteria are: presence of an idiopathic full-thickness macular hole ≥400 μm in diameter, as measured by optical coherence tomography (OCT) scans, on either or both eyes; patients electing to have surgery for a macular hole, with or without simultaneous phacoemulsification and intraocular lens implant; ability and willingness to position face-down or in an inactive face-forward position; a history of visual loss suggesting a macular hole of 12 months’ or less duration. The primary outcome is successful macular hole closure at 3 months post surgery. The treatment effect will be reported as an odds ratio with 95% confidence interval, adjusted for size of macular hole and phakic lens status at baseline. Secondary outcome measures at 3 months are: further surgery for macular holes performed or planned (of those with unsuccessful closure); patient-reported experience of positioning; whether patients report they would still have elected to have the operation given what they know at follow-up; best-corrected visual acuity (BCVA) measured using Snellen charts at a standard distance of 6 m; patient-reported health and quality of life assessed using the National Eye Institute Visual Function Questionnaire (VFQ-25).

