### Randomisation and masking

Patients are randomised in a 1:1 ratio to follow either a face-forward positioning or a face-down positioning. Randomisation is stratified by site, using random permuted blocks of size 4 or 6 in equal proportions. A secure bespoke online randomisation service implemented by the Pragmatic Clinical Trials Unit performs the randomisation. Randomisation is conducted post surgery to ensure masking the surgeon to the treatment allocated. Post surgery, trial staff input the patient’s ID and details for immediate on-screen randomisation. Randomisation is provided 7 days a week, 24 h a day. Each site is provided with a unique log-in username and password to access the service. Due to the open-label nature of the treatment, postoperative clinical staff and patients are unmasked to the treatment allocation.

Investigators assessing the primary endpoint by grading of the OCT scans are masked to the treatment allocation. In the event of any disagreement between the two clinician grades, a third independent retinal surgeon, who is also masked to the treatment allocation, will arbitrate.

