**Fig. 1 Fig1:**
[figure not shown]
Consolidated Standards of Reporting Trials (CONSORT) flowchart for the Positioning In Macular hole Surgery (PIMS) trial, with expected numbers at each stage

Baseline characteristics (variables measured preoperatively) will be summarised by positioning policy group. For continuous variables, we will examine the distribution of the data for symmetry, and report either the mean and SD, or the median and interquartile range (IQR) values. For categorical variables we will report the number and percentage in each category for categorical variables, with a note of numbers with missing data if any (see Additional file 1: Table S1).

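### No model term separates phakic eyes that kept their lens from those given a lens implant at surgery, which costs the BCVA comparison a little precision (minor)

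*SAP article*

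**What the plan says.** **Lens covariate.** In the SAP article, Variables measured and schedule of assessments, lens status is in the list that opens "The variables measured preoperatively are age, sex, ethnicity, laterality, duration of symptoms, BCVA" and is coded "lens status (either phakic or pseudophakic". Under Analysis methods, Participants, baseline is equated with preoperative: "Baseline characteristics (variables measured preoperatively) will be summarised by positioning policy group".

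**Use of the covariate.** The adjustment set is common to all outcomes: "All comparisons will adjust for linear effect of macular hole size (μm) at baseline, phakic lens status at baseline, and a random effect of site". BCVA and VFQ-25 are also adjusted for their own baseline value. The Stata commands under Analysis of primary outcome contain treatment group, hole size and lens status, with no term for lens surgery.

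**Surgery.** Patients are eligible if they choose macular hole surgery "with or without simultaneous phacoemulsification and intraocular lens implant". Lens opacity is expressly not an exclusion.

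**Order of events.** Under Randomisation and masking: "Randomisation is conducted post surgery to ensure masking the surgeon to the treatment allocated". The only stratification factor is site: "Randomisation is stratified by site, using random permuted blocks of size 4 or 6 in equal proportions".

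**The concern.** Baseline lens status groups together two kinds of phakic eye. Some still have their natural lens when randomised and at 3 months. Others had it replaced during the operation and are pseudophakic at both times. Neither the lens covariate nor any other listed variable tells them apart.

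This matters most for BCVA. Preoperative acuity reflects the macular hole together with any lens opacity. Combined surgery removes the lens component in some phakic eyes and not in others, so adjusting for preoperative BCVA cannot account for the change. That change goes into the residual. If the arms happen to differ in the share of combined surgery, it also shifts the estimated positioning difference in that particular dataset. VFQ-25 is adjusted in the same way and may be affected too.

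The definition is a matter for this document. Its section on changes from the published protocol says that lens status replaced age and sex at the suggestion of the Trial Steering Committee. The Overview notes that the pilot did not include simultaneous phacoemulsification, so a preoperative code would have been enough there. This trial allows it.

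**Working it through.** **1. The plan's own figure.** The SAP gives no figure for this point. Its sample size supplies the number analysed, so I checked that first. For 80% against 95% closure, two-sided 5% level and 85% power, with mean proportion 0.875:

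n = [1.960 × √(2 × 0.875 × 0.125) + 1.036 × √(0.80 × 0.20 + 0.95 × 0.05)]² / 0.15² = 85.7, so 86 per arm (power 0.851). Allowing for 10% loss, 86 / 0.90 = 95.6, so 96 per arm. Both stated figures reproduce, and nothing below changes them. The number analysed is 2 × 86 = 172.

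**2. Inputs for BCVA.** The document does not give them, so all are assumptions:
- f, share of eyes phakic before surgery: 0.7-0.9
- c, share of phakic eyes with combined surgery: 0.3-0.8
- d, effect of lens removal on BCVA: 0.1-0.2 logMAR
- s, residual SD once combined surgery is in the model: 0.25-0.35 logMAR

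**3. Loss of precision.** Variance left in the residual: v = f × c × (1 − c) × d². Ratio of standard errors, without and with the term: √(1 + v/s²).
- Smallest: v = 0.7 × 0.8 × 0.2 × 0.01 = 0.00112, and √(1 + 0.00112/0.1225) = 1.005.
- Largest: v = 0.9 × 0.5 × 0.5 × 0.04 = 0.009, and √(1 + 0.009/0.0625) = 1.070.

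The standard error is therefore about 0.5% to 7% larger than needed.

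**4. Chance imbalance.** The SD of the shift in the BCVA difference is √(4v/172), which runs from 0.005 to 0.014 logMAR. The standard error of the difference is 2s/√172, which runs from 0.038 to 0.053. A realised 10-point difference between arms in combined surgery would move the estimate by 0.10 × d = 0.01-0.02 logMAR.

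**5. Bias and coverage.** The BCVA model was simulated 4,000 times with 172 eyes, true effect −0.050, f = 0.8, c = 0.5, d = −0.2 and s = 0.30.

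| Model | Mean estimate | SD of estimate | 95% CI coverage |
|---|---|---|---|
| Preoperative lens status only | −0.050 | 0.0475 | 95% |
| Plus combined surgery | −0.050 | 0.0460 | 95% |

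The SD ratio is 0.0475/0.0460 = 1.033. The formula in step 3 gives √(1 + 0.008/0.09) = 1.043. The two agree roughly, given simulation error and the extra parameter that the larger model estimates.

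**6. Closure.** The planned rates imply an odds ratio of (0.95/0.05)/(0.80/0.20) = 4.75. With an assumed odds ratio of 1.5 to 2.0 for combined surgery on closure, a large simulation gave these positioning odds ratios:
- Assumed 1.5: 4.72 without the term, 4.75 with it (about 0.5% apart).
- Assumed 2.0: 4.71 without the term, 4.77 with it (about 1.4% apart).

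Expected failures are 86 × 0.20 + 86 × 0.05 = 21.5. With three fixed coefficients that is about 7 failures for each; with four, about 5.

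**The case against.** The strongest reply is that the SAP makes no error. It defines the covariate as baseline lens status, takes baseline to mean preoperative, and would record exactly that. A covariate fixed before randomisation is valid whether or not surgery later alters what it describes. This stands: a reader might infer that combined-surgery eyes are misclassified, but they are correctly coded for the variable as defined.

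A reader might also infer that the effect of lens removal biases the BCVA comparison. The document does not support that. The lens is removed before randomisation, by a surgeon who does not know the allocation, so its frequency cannot depend on the arm. The simulation shows no bias and nominal coverage. The standard error already allows for chance imbalance on average. Adjustment adds precision and protection against the imbalance that actually occurs.

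The size rests wholly on assumed inputs, and two features could make it smaller. If combined surgery is mainly a matter of site practice, stratification by site and the site effect already absorb part of it. If it goes mainly to eyes with worse preoperative acuity, the baseline adjustment absorbs part.

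Finally, this is a condensed article. The protocol or case report form may record combined surgery, and that cannot be seen here. That would make the fix easier, but the stated models would still lack the term.

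**Conclusion.** The point holds as a minor matter of precision in a secondary outcome. The stated models pool phakic eyes that kept their lens with phakic eyes made pseudophakic before randomisation, and preoperative BCVA cannot separate them. Under the assumed ranges the cost is a standard error about 0.5-7% larger than needed for the BCVA difference, with a chance shift that is small beside that standard error.

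The common adjustment set might suggest that every comparison is at risk, the primary one included. The check does not bear that out: under assumed inputs the closure odds ratio moves by about 1%, and the sample size is unaffected.

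It is still worth acting on. Combined surgery is settled before randomisation, so it is a legitimate covariate. Adding it only after an imbalance had been seen would be the kind of data-driven choice that the SAP sets out to avoid.

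**What to change.** Before unmasking, add combined lens surgery at the study operation (yes/no, from the operation record) to the BCVA model, alongside treatment group, hole size, baseline lens status, baseline BCVA and site. If combined surgery occurs only in eyes that were phakic beforehand, this is equivalent to a three-level lens status at randomisation: already pseudophakic, made pseudophakic at this operation, and still phakic. The same term may be added to the VFQ-25 model.

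Leave the primary closure model as stated. With about 21-22 expected failures, a further coefficient is hard to justify for so small a change. A rule to merge lens levels when they look sparse would bring a data-dependent choice into the primary analysis.

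The cost is one extra parameter in a linear model with about 172 patients, one data item to extract if it is not already captured, and a sentence in the SAP. Recruitment was still open when the article was submitted, so the change could be made without sight of outcomes by arm.

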## Outcome measures

The primary outcome of the study is the anatomical closure of the macular hole at 3 months post surgery.

Successful closure of the macular hole will be determined by OCT scans. The scans will be anonymised and sent to two independent retinal surgeons who will independently grade the macular hole as closed; ‘open and flat’ (without a cuff of subretinal fluid); or ‘open and elevated’ (with cuff of subretinal fluid). The readers will be masked to the identity and allocated treatment of the subject. In the event of any disparity in grading, a third independent retinal surgeon, also masked to identify and treatment allocation, will arbitrate.

The categories ‘open and flat’ (without a cuff of subretinal fluid), or ‘open and elevated’ (with a cuff of subretinal fluid) will be pooled into one category of ‘open’ for the purpose of analysis.

Secondary outcomes at 3 months post surgery are:Further surgery for macular holes, performed or planned (yes/no)Best-corrected visual acuity (BCVA) measured using a Snellen chart at a standard distance of 6 mPatient-reported experience of positioning on a scale from 0 (very difficult) to 10 (very easy)Patient-reported health and quality of life assessed using the National Eye Institute Visual Function Questionnaire (VFQ-25) from 0 (worst health and quality of life) to 100 (best health and quality of life)Patient-reported outcome ‘Given what you now know, would you still have elected to have the operation?’ with responses Yes, No or Don’t Know

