### Sample size

Clinical consensus is that face-down positioning would be recommended if there were a difference of 15% in success rates. This is the smallest clinically relevant treatment difference that we wish to detect. Previous research [6] indicates that successful closure of large macular holes without advice to position face-down occurs in 80% of cases. A study with 86 patients per group has 85% power and 95% confidence to detect a difference in outcome rate of 80% in the face-forward positioning arm versus 95% in the face-down positioning arm. With an anticipated 10% loss to follow-up, we are aiming to recruit 96 patients in each arm.

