## Analysis methods

### General analysis principles

The primary analysis for each outcome will be by intention-to-treat, meaning that all patients on whom an outcome is available will be included in the analysis, and will be analysed according to the treatment group to which they were randomised.

Through vigilance and careful planning, the PIMS trial management team aim to achieve complete capture of all data from all patients, including patients who do not adhere to the protocol or patients who withdrawal from the trial. We acknowledge that despite our best efforts, some patients may have missing data. In accordance with the intention-to-treat principle and to avoid concerns over data-driven selection methods, we state the plan for dealing with missing data here.

Missing data is a potential source of bias, and the extent and pattern of missing data can influence the interpretation of the trial. The sample size for the PIMS trial allows for a 10% loss of follow-up, and in our results we will provide a full listing of all the reasons for patients’ withdrawal of the study. This list will be helpful in justifying the assumptions that we make in regards to missing data; however, we cannot be certain that there is a relationship between observed covariates and missing outcome data, and cannot exclude the possibility of some data missing not at random.

We will analyse the data without undertaking any sensitivity analysis if the primary outcome is missing in fewer than 5% of cases (nine patients or less). If more than nine patients’ primary outcome is missing, we will undertake sensitivity analysis to test if the missing at random assumptions are appropriate. We will use a pattern-mixture approach to model the consequences of a systematic difference between missing and nonmissing values, to see if the conclusions drawn from the PIMS study are affected when the missing-at-random assumption is violated.

All analyses will be performed using Stata (Stata Corporation, College Station, TX, USA).

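### Patients re-operated before 3 months are excused from the secondary questionnaires, so the patient-reported comparisons lose some surgical failures, and no missing-data analysis covers the loss

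*SAP article*

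**What the plan says.** The section Variables measured and schedule of assessments describes how an early failure comes to light: "Patients have a 2-week postoperative appointment, at which time clinicians may be able to identify that the macular hole closure was unsuccessful". It then sets two rules for patients who are re-operated early. For the primary outcome, "The outcome of any participant who had a second surgery after randomisation but before the 3-month visit will be imputed as open". For the patient-reported outcomes, "These patients will not be completing secondary questionnaires".

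Three of the five secondary outcomes listed under Outcome measures are patient-reported: the VFQ-25, the 0 to 10 score for experience of positioning, and the question "would you still have elected to have the operation". The article uses the word questionnaire by name only for the VFQ-25. The plural in the rule suggests that the other two items are covered as well, but this is an inference.

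General analysis principles states the aim of "complete capture of all data from all patients, including patients who do not adhere to the protocol". The same section defines intention-to-treat as analysing, as randomised, everyone who has the outcome. It requires a missing-data sensitivity analysis, by a pattern-mixture approach, only when the primary outcome is missing in more than nine patients.

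**The concern.** The rule removes patients from a randomised comparison because of something that happens after randomisation and is itself a failure of the first operation. Those who remain are selected towards success. If failure or early re-operation differs between arms, they are selected differently in each arm, and an analysis of available cases no longer compares like with like.

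The loss is also planned. These patients have not withdrawn, yet the plan excuses them from giving data that it elsewhere aims to capture from everyone. Nothing in the plan addresses the result: because their primary outcome is set to open, re-operated patients never count towards the trigger of nine, and no missing-data analysis is specified for the secondary outcomes.

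At stake are how patients see, how they found the positioning, and whether they would choose the operation again. These bear directly on the informed choice that the trial sets out to support.

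**Working it through.** **1. The plan's own figure.** Sample size states: "A study with 86 patients per group has 85% power and 95% confidence", for "80% in the face-forward positioning arm versus 95% in the face-down positioning arm". With a two-sided 5% level, pooled variance and no continuity correction, n = [1.960·√(2 × 0.875 × 0.125) + 1.036·√(0.80 × 0.20 + 0.95 × 0.05)]² / 0.15² = 85.7, so 86 per arm (power 0.851). Then 86/0.90 = 95.6, so 96, which agrees with "With an anticipated 10% loss to follow-up, we are aiming to recruit 96 patients in each arm". The planning rates are therefore a sound base for what follows.

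**2. Expected failures at those rates.** With 86 followed up per arm: 86 × 0.20 = 17.2 face-forward and 86 × 0.05 = 4.3 face-down. The face-forward share is 17.2/21.5 = 80%.

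**3. What the rule leaves.** Let f be the failure rate (0.20 or 0.05) and r the share of failures re-operated before the 3-month visit, taken as equal in both arms. The documents do not give r, so a range is shown. Questionnaires lost per arm = 86·f·r. Failure share among those who answer = f(1 − r)/(1 − f·r). If failures score D worse than closures, the true contrast through closure is 0.15·D, and the observed contrast is the difference in failure shares times D.

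| r | Lost, face-forward / face-down | Failure share among answerers | Difference | Kept (÷ 0.15) |
|---|---|---|---|---|
| 25% | 4.3 / 1.1 | 0.1579 / 0.0380 | 0.1199 | 80% |
| 50% | 8.6 / 2.15 | 0.1111 / 0.0256 | 0.0855 | 57% |
| 75% | 12.9 / 3.2 | 0.0588 / 0.0130 | 0.0458 | 31% |
| 100% | 17.2 / 4.3 | 0 / 0 | 0 | 0% |

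For an assumed D of 10 points on the raw VFQ-25 scale, the contrast is 1.5 points with full collection, against 1.2, 0.85, 0.46 and 0. The SAP analyses a transformed score, so these points only illustrate the size.

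**4. Equal closure.** With 80% closure in both arms and equal r, the losses match (8.6 v 8.6 at r = 50%) and this rule creates no contrast. If r differed, say 50% face-forward and 25% face-down (assumed), the failure shares among answerers would be 0.1111 and 0.1579, a false contrast of 0.0468·D.

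Absolute results shift even when the arms balance. Assume that 95% of patients with closed holes and 50% of failures would choose surgery again. The true figure at 80% closure is 0.80 × 95 + 0.20 × 50 = 86%. At r = 50% the trial sees 95 − 45 × 0.1111 = 90%, and at r = 100% it sees 95%.

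**5. Positioning experience.** This score depends directly on the allocated posture. Assume that face-down is 2 points harder and that failures score 2 points lower. At the planning closure rates, face-down minus face-forward is −2 + 2 × 0.15 = −1.70 with full data, −2 + 2 × 0.0855 = −1.83 at r = 50%, and −2.00 at r = 100%. Here the exclusion moves the estimate away from no difference.

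**The case against.** A reader might infer that the lost patients are bound to come mostly from the face-forward arm and that all three patient-reported comparisons are biased towards no difference. The documents do not support that. The 80% v 95% split is the hypothesis under test; with equal closure and equal early re-operation the losses balance. Step 5 shows one outcome where the estimate can move the other way. Postoperative staff are unmasked, so early re-operation could itself differ by arm, which makes the direction less certain still.

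Nor can one say that effects acting through closure are removed, or that patients with failed surgery are never asked. That is true only at r = 100%. The 2-week visit is said only to make detection of failure possible, and the further-surgery outcome includes operations still planned at 3 months. Failures not yet re-operated therefore do answer.

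The defence can add that the primary and further-surgery outcomes are not lost under this rule, that BCVA is not a questionnaire, that the trial is powered on closure alone, and that the SAP will report the number analysed per arm for each comparison. All of this stands and lowers the severity. It does not answer the central point. A count of patients analysed shows that data are missing, but not that failure caused it, and no analysis is planned for the gap.

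**Conclusion.** The point holds in conditional form. The rule excludes some surgical failures from the VFQ-25, and apparently from the other two patient-reported outcomes. It contradicts the stated aim of complete capture, and no missing-data sensitivity analysis covers it.

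Under the planned closure rates, and with early re-operation of failures equally likely in both arms, about four in five of the patients lost would be face-forward. The contrast acting through closure would shrink to about 80%, 57%, 31% or 0% of its true size as r goes from 25% to 100%. For the VFQ-25 and the re-election question this means attenuation only if failures also report worse outcomes. If closure is equal, the losses balance only when early re-operation does not differ by arm, and absolute results are still too favourable if failures fare worse. For positioning experience the bias may go in either direction.

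This should be fixed, but it does not threaten the primary result.

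**What to change.** Delete the sentence. Collect the existing questionnaires from every randomised patient at the scheduled 3-month time, whatever their re-operation status, and analyse them as randomised. Using the same time point for everyone keeps the timing of assessment from depending on failure.

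Report by arm the number of questionnaires missing because of re-operation.

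For patients already missed, add a pattern-mixture sensitivity analysis for these outcomes over a stated range of values in both directions. It should not be tied only to failures who were not re-operated: that group shrinks as r rises and is empty at r = 100%.

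The cost is small: a change of wording and existing forms for at most about 21 or 22 patients at the planning rates (17.2 + 4.3 = 21.5 at r = 100%). Recruitment was still open when the article was submitted, so later patients can be covered. The downside is that 3-month answers from re-operated patients will reflect a recent second operation, but this is part of the effect of the allocated policy.
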